**Methods::**

In this randomized controlled study, a total of 236 eligible patients will be assigned to the experimental group (n = 118) or the control group (n = 118) in a 1:1 ratio. The control group will be taken mesalazine enteric-coated tablets combined with placebo enema and the experimental group will be taken mesalazine enteric-coated tablets combined with KFX enema. Participants will receive 8 weeks of intervention treatment and 3 months of maintenance treatment before pregnancy. The primary assessment is the Mayo score. Secondary outcomes include mucosal healing, faecal calprotectin (FC), Inflammatory Bowel Disease Quality (IBDQ), and pregnancy outcome.

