In recent years, there has been an increasing amount of study on the impact of the female with UC on pregnancy and neonatal. Many pieces of evidence show that pregnant women with UC have a higher incidence rate of abnormal pregnancy and delivery, such as the delivery of premature, low birth weight infants, and venous thromboembolism (VTE) risk in both pregnancy and the postpartum period than those without UC, and there are significant differences in active UC.^[5–7]^ Furthermore, female with UC increased the risk of infant birth defects overall. In a retrospective cohort study^[8]^ of 7798 cases of UC in Quebec, Canada between 1989 and 2016, UC was associated with 1.53 times the risk of central nervous system defects. Another study^[9]^ concluded that neonatal are at an elevated risk of limb and urinary defects. The problem about the damages of UC medication to their unborn children or heredity increases their fertility concerns.^[10]^ Guideline^[10]^ recommends that women plan to get pregnant when in remission. However, it cannot be ignored that an increased risk for UC relapse during pregnancy^[11]^ Similarly, a meta-analysis^[12]^ by Abhyankar et al has demonstrated that the recurrence rate and severity of UC influenced by disease activity at the time of conception. In addition, several lines of evidence suggest that UC has an interactive relationship with Anxiety and Depression (A&D). Individuals with UC are at increased risk of A&D. Meanwhile, UC with comorbid A&D are more challenging to manage. The selective protective effect of antidepressant treatment on UC confirms that it has a two-way relationship with A&D^[13,14]^ A prospective cross-sectional study^[15]^ in the United States or Denmark suggest that activity UC significantly correlated with sexual dysfunction. Besides, it exacerbates dysmenorrhea and gastrointestinal symptoms during menstruation.^[16]^ Overall, for females with UC, there are unique challenges in a different decade of life, spanning from menstruation, sexual health, mental health to fertility, and pregnancy. Consequently, It is essential for the patients to have optimal management of UC prior to and during pregnancy to achieve favorable maternal and neonatal outcomes, and preferable quality of life.^[17]^

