### Inclusion criteria

2.4

Patients who meet all of the following conditions will be considered for enrollment. The inclusion criteria are as follows:

1.Females, aged between 20 and 45 years;2.Patients who meet the criteria of active UC refer to Chinese consensus on diagnosis and treatment;3.Patients preparing for pregnancy;4.Patients who willing to participate in the study, sign an informed consent and can be followed up

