### Exclusion criteria

2.5

The exclusion criteria are as follows:

1.Patients with infertility caused by diseases of reproductive system organs or male infertility2.Patients with intestinal organic diseases and other serious complications such as local stenosis, intestinal obstruction, intestinal perforation, colon cancer, colorectal cancer, bacillary dysentery, Amoebic dysentery, chronic schistosomiasis, radiation enteritis, etc.3.Patients with the allergic constitution or allergic to any known medicine components of Mesalazine or KFX4.Patients with serious diseases such as liver, kidney, hematopoietic system and mental disorder

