## Interventions

3

In the experimental group, mesalazine enteric-coated tablets (supplied by LOSAN Pharma GmbH 0.5 g/tablet) will be taken orally 1.0 g per time and 3 times a day for 8 weeks continuously. At the same time, the KFX (supplied by Sichuan Good doctor Panxi Pharmaceuticals) will be given retention enema treatment 100 mL per time, 1 time a day. KFX need to be heated to 37°C and poured into a one-time enema bag. The enema tube will be inserted into the anus for about 10 cm. The control group enteric-coated mesalazine tablets will be taken orally 1.0 g per time and 3 times a day for 8 weeks. The enema method of placebo is the same as that of the treatment group. During the treatment period, patients in both groups avoid irritant and crude fiber food and supplemented with an adequate amount of folic acid (2 mg/d). Eight weeks later, according to the guidelines,^[17]^ UC patients in remission (Mayo score ≤2 and normal intestinal mucosa or no active inflammatory) will continue to be treated with maintenance therapy Maintenance therapy is based on the treatment mentioned above, but the dose is reduced (mesalazine 0.5 g/time, 3 times/day, KFX/placebo enema 50 mL) for 3 months. Subsequently, the patient in stable condition will be given active pregnancy guidance. Both groups of patients change to oral mesalazine (0.5 g/time, 3 times/day) from pregnancy to delivery. Due to a lack of research on the safety of KFC being used during pregnancy, KFX will be discontinued once patients in remission enter the active pregnancy preparations stage. All drugs should be the same lot number. In the course of the study, it is forbidden to add other drugs or interventions that may interfere with the trial. Cases in which symptoms have not alleviated or even aggravated, the participants voluntarily withdrew, and no medication or any follow-up records due to poor compliance will be regarded as excluded cases, and participants will be required to complete the assessments as much as possible.

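### Inclusion criterion 3 does not require that women are not pregnant and will defer conception, and no pregnancy test is named before visit ⑤, although KFX and colonoscopy fall in weeks 1 to 20

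*Protocol article*

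**What the plan says.** **Who enters.** Section 2.4 lists four inclusion criteria, all of which must be met. Criterion 2 is "Patients who meet the criteria of active UC refer to Chinese consensus on diagnosis and treatment" and criterion 3 is "Patients preparing for pregnancy". The others cover age (20 to 45 years) and willingness to consent and be followed. Section 2.5 lists four exclusions, of which the only reproductive one is "Patients with infertility caused by diseases of reproductive system organs or male infertility".

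**What they receive.** Section 3 gives KFX or placebo as a daily 100 mL enema for 8 weeks, then 50 mL for 3 months in women who reach remission. Table 1 places maintenance in weeks 9–20. The abstract summarises this as "8 weeks of intervention treatment and 3 months of maintenance treatment before pregnancy".

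**When KFX stops.** Section 3 states that "KFX will be discontinued once patients in remission enter the active pregnancy preparations stage", and gives the reason: "Due to a lack of research on the safety of KFC being used during pregnancy". It adds: "Both groups of patients change to oral mesalazine (0.5 g/time, 3 times/day) from pregnancy to delivery".

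**What is measured.** Table 1 marks the Mayo score and mucosal healing at visits ①, ③ and ④. The Mayo score has a colonoscopy item (Table 2). Section 4.2 urges caution with endoscopy in pregnancy and substitutes faecal calprotectin (FC) once a woman is pregnant. The pregnancy-outcome row of Table 1 is marked only at visits ⑤–⑦. Section 4.3 names the safety tests, including routine urine testing, at baseline, week 8 and week 20. A pregnancy test is not among them.

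**The concern.** The trial selects women because they want to conceive, and section 2.5 removes couples with specified causes of infertility. It then gives them, for up to 20 weeks, a product that the protocol itself says has not been adequately studied in pregnancy. Safe conduct depends on these women not conceiving until the enema has stopped. That condition can be inferred from the order of the treatment periods, but it is not a condition of entry and no listed test checks it.

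What is at stake is KFX exposure, and colonoscopy, in a pregnancy that nobody has recognised. The two protections the article does provide, the move to oral mesalazine alone and FC in place of endoscopy, can be applied only once a pregnancy is known.

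**Working it through.** The plan gives no figure on this point, so the check sets the sections against one another.

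**1. Is the intended order clear?** Yes. The abstract places both treatment periods before pregnancy. Section 3 runs 8 weeks of treatment, then 3 months of maintenance for women in remission, then pregnancy guidance for those who are stable, with KFX stopped as active preparation begins.

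**2. Does eligibility secure it?** None of the four inclusion criteria mentions non-pregnancy, contraception or deferral. None of the four exclusions mentions current pregnancy.

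**3. Does the schedule secure it?**

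| Time | KFX/placebo | Colonoscopy-based assessment | Pregnancy test named |
|---|---|---|---|
| Visit ①, 4 weeks before treatment | none | yes | no |
| Visit ②, day 0 | about to start | no | no |
| Visit ③, weeks 1–8 | 100 mL daily | yes | no |
| Visit ④, weeks 9–20 | 50 mL, women in remission | yes | no |
| Visits ⑤–⑦, pregnancy | stopped | no (FC instead) | pregnancy outcome recorded |

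No pregnancy test is named at any of visits ①–④.

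**4. Do the stopping rules cover conception in weeks 1–20?** Only partly. The KFX stopping sentence concerns women in remission who reach the preparation stage; it does not address conception during treatment. The mesalazine sentence can be read to cover any recognised pregnancy, but it provides no means of recognising one.

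**5. Where would a test help?** A screening test may be 4 weeks old when dosing starts. A test at week 8 comes after 8 weeks of enema, and one at week 20 after a further 12 (8 + 12 = 20). Tests at weeks 8 and 20 therefore protect the colonoscopy and stop further dosing; they do not prevent early exposure. Early exposure is prevented by the agreement to defer and by a test immediately before the first enema.

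**6. Does this touch the statistics?** No. The sample size in section 2.6 uses only the two effective rates, the significance level, power and dropout. It reproduces as 107.5 per group before dropout, and 107.5 × 1.1 = 118.3 against the stated 118. No pregnancy quantity enters.

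**The case against.** The strongest reply is that this is a condensed article. Pregnancy testing and advice on deferral are routine content of a full protocol and consent form, neither of which is shown. The clinical examination in Table 1 and the routine examination and urine test in section 4.3 are not itemised, so a pregnancy test may exist. This stands as a limit: the finding concerns what the article lists, not what the site does. It does not dispose of the point, because an article normally prints its eligibility lists in full. These lists are detailed enough to name individual infections, yet they leave out the condition on which the treatment sequence depends.

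It can also be said that a woman preparing for pregnancy is ordinarily not yet pregnant, and that deferral is implied by the order in section 3 and by the Introduction, which cites a guideline that "recommends that women plan to get pregnant when in remission". Both are fair and keep the point minor. Guidance given after maintenance is still not a requirement at entry.

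Three stronger readings are tempting, and the documents do not support them.

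- A reader might infer that criterion 3 contradicts section 3, since women seem to enter in the very state at which KFX must stop. But the stopping stage is defined for patients in remission, whereas criterion 2 requires active disease at entry. The two stages differ, and the abstract and section 3 already put pregnancy after maintenance.
- A reader might multiply 118 or 236 women by the weeks of enema or the number of colonoscopies and take the total as the size of the problem. Such totals are only sample size times schedule, and would be the same if nobody conceived.
- A reader might estimate conceptions during treatment. The documents give no conception rate and no proportion who would defer, so any count would rest on outside assumptions.

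**Conclusion.** The point holds as a minor patient-safety gap in how criterion 3 is written. The protocol intends KFX to finish before conception and says why, but the listed criteria require neither non-pregnancy nor deferral, and no pregnancy test is named before visit ⑤. The size in exposed conceptions cannot be derived from the documents and would be zero if every woman defers. The primary analysis and the sample size are unaffected. The conclusion assumes that the printed eligibility lists are complete; if the full protocol already contains these conditions, only the published wording needs correction.

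**What to change.** Reword criterion 3 to: *planning pregnancy after completing study treatment, not currently pregnant, and agreeing to defer conception until KFX/placebo is stopped*.

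Add a Table 1 row for a urine pregnancy test immediately before the first enema and before the week-8 and week-20 colonoscopies, using urine already collected under section 4.3 where possible. The pre-enema test may need a fresh sample on day 0.

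On a positive result, stop the enema in either arm (which needs no unblinding), continue oral mesalazine, use FC instead of endoscopy, and move the woman to the visit ⑤–⑦ follow-up. Her Mayo score would then lack its colonoscopy item and would fall under the missing-data method already named in section 4.5.

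The cost is one reworded criterion, one schedule row and an inexpensive test. The downside is that a few women unwilling to defer may decline to enrol.

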### Exclusion criteria

2.5

The exclusion criteria are as follows:

1.Patients with infertility caused by diseases of reproductive system organs or male infertility2.Patients with intestinal organic diseases and other serious complications such as local stenosis, intestinal obstruction, intestinal perforation, colon cancer, colorectal cancer, bacillary dysentery, Amoebic dysentery, chronic schistosomiasis, radiation enteritis, etc.3.Patients with the allergic constitution or allergic to any known medicine components of Mesalazine or KFX4.Patients with serious diseases such as liver, kidney, hematopoietic system and mental disorder

### Sample size

2.6

The sample size was determined by the primary study results. According to previous reports, the effective rate of the experimental group based on the Mayo, score ranges from 57.5% to 76.47%,^[35,36]^ and the average rate is about 66.99%. The effective rate of the control group ranges from 41.25% to 55.65%,^[22,37]^ and the average rate is about 48.45%. We will use the following formula to estimate sample size:$${\text{n}}_{\text{c}}=\frac{[\pi_{t}(1-\pi_{t})/k+\pi_{c}(1-\pi_{c})]{\left(u_{1-\partial /2}+u_{1-\beta }\right)}^{2}}{{\left(\pi_{t}-\pi_{c}\right)}^{2}}$$

With a 5% significance level (α = 0.05), 80% Power (β = 0.2), and 10% dropout rate, at least 118 patients should be enrolled in each group and 236 total participants will be recruited.

### Randomization and blinding

2.7

Participants will be randomly allocated according to a random list of numbers generated with SPSS21.0 software. Opaque envelopes containing an allocation sequence number will be used by an independent staff who needs to prepare the assignments and conceal the allocation sequence. Blinding will be strictly maintained to intervention staffs, participants, the statistician, and staff who obtained outcome measurement. They will not know the corresponding relations between numbers and different groups. By using an identical liquid placebo in color, consistency, and smell to the KFX, blinding will be ensured.

## Interventions

3

In the experimental group, mesalazine enteric-coated tablets (supplied by LOSAN Pharma GmbH 0.5 g/tablet) will be taken orally 1.0 g per time and 3 times a day for 8 weeks continuously. At the same time, the KFX (supplied by Sichuan Good doctor Panxi Pharmaceuticals) will be given retention enema treatment 100 mL per time, 1 time a day. KFX need to be heated to 37°C and poured into a one-time enema bag. The enema tube will be inserted into the anus for about 10 cm. The control group enteric-coated mesalazine tablets will be taken orally 1.0 g per time and 3 times a day for 8 weeks. The enema method of placebo is the same as that of the treatment group. During the treatment period, patients in both groups avoid irritant and crude fiber food and supplemented with an adequate amount of folic acid (2 mg/d). Eight weeks later, according to the guidelines,^[17]^ UC patients in remission (Mayo score ≤2 and normal intestinal mucosa or no active inflammatory) will continue to be treated with maintenance therapy Maintenance therapy is based on the treatment mentioned above, but the dose is reduced (mesalazine 0.5 g/time, 3 times/day, KFX/placebo enema 50 mL) for 3 months. Subsequently, the patient in stable condition will be given active pregnancy guidance. Both groups of patients change to oral mesalazine (0.5 g/time, 3 times/day) from pregnancy to delivery. Due to a lack of research on the safety of KFC being used during pregnancy, KFX will be discontinued once patients in remission enter the active pregnancy preparations stage. All drugs should be the same lot number. In the course of the study, it is forbidden to add other drugs or interventions that may interfere with the trial. Cases in which symptoms have not alleviated or even aggravated, the participants voluntarily withdrew, and no medication or any follow-up records due to poor compliance will be regarded as excluded cases, and participants will be required to complete the assessments as much as possible.

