### Study design

2.1

This study is designed as a randomized, controlled, double-blind trial. With mesalazine enteric-coated tablets as the control, to explore the efficacy of mesalazine combined with KFX enema in the treatment of active UC in women with fertility requirements and to improve pregnancy outcome and quality of life, reduce the recurrence rate. Prospective participants will be asked to talk face to face with the researcher for a baseline screening visit after diagnosis. After the 8 weeks of treatment, they will be followed for another 3 months of maintenance therapy. This study will start in October 2020 and continue until April 2022. The study schedule is detailed in Table 1. The flowchart of the trial is shown in Figure 1.

**Table 1 T1:** Data collection points.

	Screening	Randomization	treatment	Follow-up (maintenance therapy)	Follow-up (pregnancy until delivery)		
Visits	①	②	③	④	⑤	⑥	⑦
Time point	4 weeks before treatment	Day 0	Weeks 1–8	Weeks 9–20	Months 0–3	Months 4–6	Months 7 to delivery
Age	X						
Duration of disease	X						
Disease history	X						
Comorbidity	X						
Clinical examination	X						
control group							
experimental group							
Mayo score	X		X	X			
Mucosal healing	X		X	X			
IBDQ	X		X	X	X	X	X
Faecal calprotectin	X		X	X	X	X	X
pregnancy outcome					X	X	X
Adverse events			X	X	X	X	X
Causes of dropout			X	X	X	X	X
Data analysis							X

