### Secondary outcomes

4.2

The secondary outcomes include:

1.pregnancy outcomePregnancy outcome include pregnancy rate (%), abnormal pregnancy rate (%), and live birth rate (%). In this study, abnormal pregnancy is defined as any of the following: abortion, threatened abortion, premature delivery, delivery of a low-birth-weight infant, VTE, and congenital defect, etc—any pregnancy-related event causing illness in the mother or fetus.2.mucosal healing rate (%)Patients with remission UC can be seen as normal colon mucosal appearance, pseudopolyp formation, or scar-like changes.3.IBDQThe patients’ quality of life is evaluated by the IBDQ^[39]^ included the 32 items and divided into 4 modules: bowel symptoms, systemic symptoms, emotional function, and social function. Each question has graded responses from 1 to 7, and thus scored from 32 to 224 points, with a higher score indicates a better quality of life.4.FCEndoscopies as the “gold standard” determine the presence of mucosal inflammation in the bowel. Some studies propose that endoscopy should be used with caution during pregnancy to avoid adverse pregnancy outcomes.^[40,41]^ Therefore, for the noninvasive monitoring of the activity or relapse of UC, the FC will be measured to replace endoscopyat after pregnancy. The concentration of FC has a strong correlation with the level of intestinal inflammatory activity during pregnancy.^[42]^

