### Statistical analysis

4.5

The statistician performs Statistical analyses of data by using SPSS21.0 software (International Business Machines Corp., Armonk, NY). Intention-to-treat principle approach for efficacy and safety analysis will be used. As dealing with the missing values, multiple imputations method will be applied. Continuous variables with normal distribution, expressed as Mean ± Standard Deviation, will be analyzed by *t* test. In contrast, nonparametric tests will be adopted when variables are kept in the abnormal distribution. Categorical data presented by frequency and percentage will be analyzed by the chi-square test or Fisher exact test. All the tests will be conducted two-sided, and a *P*-value < .05 will be considered as the significant level.

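### KFX is given only by rectal enema, but the plan makes no stated use of disease extent; record it at screening and use it in the main comparisons

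*Protocol article*

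**What the plan says.** - **Treatment (section 3, Interventions).** Oral mesalazine is the same in both arms, so the contrast is KFX against placebo enema. During the 8 weeks KFX "will be given retention enema treatment 100 mL per time, 1 time a day". In the 3-month maintenance phase the volume becomes "KFX/placebo enema 50 mL". On delivery the section says: "The enema tube will be inserted into the anus for about 10 cm". It does not say how far the retained fluid spreads.
- **Eligibility (sections 2.4 and 2.5).** The disease criterion is "Patients who meet the criteria of active UC refer to Chinese consensus on diagnosis and treatment". No inclusion or exclusion criterion refers to extent.
- **Baseline data (Table 1).** The screening rows include age, "Duration of disease", disease history, comorbidity, clinical examination and the Mayo score. Extent has no row.
- **Randomisation (section 2.7).** "Participants will be randomly allocated according to a random list of numbers generated with SPSS21.0 software". No stratification factor is stated.
- **Outcomes (sections 4.1 and 4.2).** The Mayo score has a colonoscopy item that grades severity, not extent. Mucosal healing is described as "normal colon mucosal appearance, pseudopolyp formation, or scar-like changes".
- **Analysis (section 4.5).** Continuous outcomes get a t test or a nonparametric test. Categorical outcomes "will be analyzed by the chi-square test or Fisher exact test". No covariate appears.

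**The concern.** Extent is the baseline feature most directly tied to how much of the disease a rectal treatment can contact. The outcomes, in contrast, describe the colon as seen at colonoscopy and the patient's overall condition. A woman with inflammation confined to the rectum and a woman with inflammation of the whole colon enter the same unadjusted comparison, although the enema may reach very different shares of their disease.

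Two things are at stake. First, if benefit depends on contact, the average effect over all enrolled women may fall short of the planned 18.54 points. A null result could then mean either that KFX does not work or that it works only in distal disease, and the listed data and tests offer no means of looking further. Second, if extent is also prognostic, leaving it out of the comparison gives up some precision in a design with no reserve.

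**Working it through.** **Inputs.** From section 2.6: effective rates of 66.99% (experimental) and 48.45% (control), two-sided α = 0.05, 80% power, 10% dropout, 118 per arm. The calculation uses the effective rate because the sample size rests on it.

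**Reproducing the plan's figure.** The variance sum is V = 0.6699×0.3301 + 0.4845×0.5155 = 0.4709. Then n = 0.4709×(1.960+0.842)²/0.1854² = 107.5 per arm. Multiplying by 1.1 gives 118.3, which matches 118. Dividing by 0.9 gives 119.5, so 120. The plan's arithmetic holds, with nothing to spare.

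**Baseline power.** Evaluable women: 118×0.9 = 106 per arm. SE = √(0.4709/106) = 0.0667. Power = Φ(0.1854/0.0667 − 1.96) = Φ(0.82) = 79%.

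**Possible dilution.** The article gives no extent distribution. Assume that a share q of women lie beyond the enema's reach and that the full 18.54 points apply to the others. If women beyond reach gain nothing, the overall difference is 18.54×(1−q). If they keep half the effect, it is 18.54×(1−q/2). If the rates in section 2.6 already come from a comparable extent mix, nothing is lost.

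| q | Power, no loss | Power, half effect beyond reach | Power, no effect beyond reach | Power, within-reach women only |
|---|---|---|---|---|
| 10% | 79% | 75% | 70% | 75% |
| 20% | 79% | 70% | 59% | 70% |
| 30% | 79% | 65% | 48% | 64% |
| 40% | 79% | 59% | 37% | 58% |

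The last column uses 106×(1−q) women per arm at 18.54 points. It beats the whole-group analysis only under the no-effect assumption. With half the effect retained, the two are about equal.

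**Chance imbalance.** With 118 per arm, the 95% range for the difference in the share with extensive disease is ±1.96×√(2q(1−q)/118). That is ±10 points at q = 20% and ±13 points at q = 50%. If extensive disease lowers the effective rate by g = 10 to 30 points (assumed), the edge of that range moves the rate difference by 1 to 4 points (0.102×0.10 = 0.010; 0.128×0.30 = 0.038). The unadjusted SE of 6.7 points already contains this variation.

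**Gain from adjustment.** Stratifying by extent removes the between-category part of the variance, so V becomes V − 2q(1−q)g².
- q = 20%, g = 10 points: V = 0.4709 − 0.0032 = 0.4677, SE = 0.0664, power 79.7%.
- q = 50%, g = 30 points: V = 0.4709 − 0.0450 = 0.4259, SE = 0.0634, power 83.3%.

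The gain is therefore about 0.3 to 4 percentage points of power.

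**Power for treatment by extent.** Suppose the whole effect lies in one of two categories, so the interaction is 18.54 points. Its SE is about √(V/(106·q(1−q))).
- q = 20%: SE = 0.167, power = Φ(1.11 − 1.96) = 20%.
- q = 50%: SE = 0.133, power = Φ(1.39 − 1.96) = 28%.

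**The case against.** The strongest reply has four parts.

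- **Dilution is not shown.** A reader might infer that disease beyond 10 cm is out of reach and that power must therefore drop, perhaps to 37%. The documents do not support this. Tube depth is not fluid reach, nothing says that KFX acts only on mucosa it touches, and section 2.6 does not give the extent mix of the studies behind its rates. If those studies enrolled a similar mix, the planned effect is already the diluted one. This objection stands.
- **All active UC is a legitimate target population.** The average effect over that population is then the quantity of interest, and a smaller average is not a bias. This also stands, and adjustment would not restore an average that is truly smaller.
- **Chance imbalance is not a flaw in a randomised comparison.** A reader might take unadjusted imbalance for bias. It is not: the test is valid and its standard error allows for the imbalance. Only the loss of precision remains, and it is modest.
- **This is a condensed article.** Disease history or the screening colonoscopy report may capture extent, and covariates may be set out in a full protocol or SAP. This stands in part: the article cannot show that extent goes unrecorded. But section 4.5 does name the tests, and they are unadjusted, so extent would go unused in the stated comparisons even if it were recorded.

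**Conclusion.** The concern holds in a limited form. For a treatment given only by the rectal route, the article makes no stated use of disease extent in eligibility, listed baseline data, randomisation or analysis, and it fixes unadjusted tests. There is no arithmetic error and no bias in the primary comparison.

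The quantified benefit of correcting this is small: power of 80–83% instead of about 79%, assuming a prognostic gap of 10 to 30 points and an extensive share of 20% to 50%. The larger power losses in the table are conditional scenarios whose lower end is zero, so they should not be read as a forecast. The main gain is interpretive. With extent recorded, a null or weak result can at least be described by extent, though not resolved, given interaction power of only about 20–28%. Because the change costs almost nothing, it is worth making.

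**What to change.** Leave eligibility, treatment and sample size as they are.

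1. Record the maximal extent of inflammation in pre-defined categories (proctitis, left-sided, extensive) from the screening colonoscopy that the Mayo score already needs. Section 5.1 reports that recruitment is under way, so take extent from existing reports for women already randomised.
2. Before unblinding, replace the unadjusted tests of the Mayo and mucosal-healing outcomes in section 4.5 with a comparison stratified by, or adjusted for, extent category. A stratified risk difference for rates, or a linear model with an extent term for scores, keeps the target as the average effect over all enrolled women.
3. Pre-specify the treatment-by-extent estimate with its confidence interval as supportive only, and state its low power.
4. State in section 2.6, if known, the extent mix of the studies behind the 66.99% and 48.45% rates.

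The cost is one case record form field, one or two degrees of freedom in the analysis, and a supportive estimate with a wide interval.
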